A parenting support programme will be offered that focuses on social and emotional well-being called PACT Online, grounded in Acceptance and Commitment Therapy. It has been tested with parents of children diagnosed with or with a high likelihood of neurodevelopmental disability or developmental delay and was designed to be flexible and appropriate to supporting all parents.^27^ This programme is directly offered to parents at 3 months CA, but families can self-refer at any point during the study (figure 2, online supplemental figure 1). Within this study, a First Nations PACT Online package will be codesigned. For infants aged <12 months CA in the study who have a high chance of adverse neurodevelopmental disability including cerebral palsy, autism or fetal alcohol spectrum disorder, a referral will be offered to families to participate in the Learning through Everyday Activities with Parents Study (LEAP) (figure 2, online supplemental figure 1). LEAP is a randomised early support trial delivered in the home by Indigenous family support workers. Compared with a health advice programme, it includes goal-directed skill training, responsive parenting, environmental enrichment through learning games and parent educational modules.^28 29^

At regular intervals, data linkage between the SFS database and the LEAP and PACT Online teams will take place to enable analysis of the family support programmes within the context of the SFS study. To ensure accurate referral processes, parents’ samples and questionnaires will be regularly reviewed for signs of clinically relevant findings or having an increased chance of developing a clinically relevant disease (see online supplemental figure 1 on flow chart for infant testing and referral processes in the SFS). Where family support programmes are required but outside the scope of the study, access to services, including liaising with the primary care team, will be facilitated by the study team.

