##### Sample size and statistical power

The sample size of 400 families followed prospectively was chosen to provide sufficient power to examine associations between perinatal strengths/risk factors and pregnancy, birth and early childhood outcomes. Assuming approximately 5% of the cohort will have the primary outcome of ‘chance of cerebral palsy/autism spectrum disorder/neurodevelopmental outcome’, this sample gives 80% power (α=0.05) to detect absolute differences of ≥8 percentage points between binary risk factor groups. For more common binary outcomes, differences of >28% can be detected. For continuous outcomes, we will be able to identify between-category differences of >0.3 SD (Z-score units). These estimates are conservative, as repeated measurements over time and mixed-effects models will further improve precision.

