##### Statistical analysis

To examine relationships between perinatal strengths/risk factors and continuous outcomes (eg, Kimberley Mum's Mood Scale (KMMS)), we will use linear or mixed effects regression for repeated measures. Binary outcomes will be analysed using logistic regression, and count outcomes with Poisson or other suitable count models. Analyses will account for the multi-site teletrial design by adjusting for clustering at the site/community level (eg, through random or fixed effects or robust standard errors). For multivariable modelling, candidate predictors will be screened individually, with final model selection guided by Bayesian Information Criteria. Model calibration will be checked graphically, and internal validation performed via bootstrap resampling.

Missing data will be treated case-by-case using multiple imputation when data are plausibly missing at random, and pattern mixture methods with sensitivity analyses when not missing at random mechanisms are likely. Longitudinal mixed-effects models will use all available observations under missing at random assumptions. If differential loss to follow-up occurs, we will apply weighting-based sensitivity analyses (eg, inverse probability of follow-up weighting). Each analysis will include appropriate adjustments for multiple comparisons to balance type I and II error risks.

For the PACT Online and LEAP programmes, effectiveness will be investigated using mixed effects models with programme participation included as the main effect and models adjusted for baseline factors. Differences in characteristics of families who do and do not participate in the programmes will be assessed. If any differences exist, they will be adjusted for in analyses using weighting methods such as propensity matching. Cohort embedded summaries of eligibility, referral and uptake will be reported descriptively. The sensitivity of observational comparisons (eg, uptake vs non-uptake) will be assessed.

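### LEAP is randomised and limited to high-chance infants, yet the plan estimates its effectiveness by programme participation, which is confounded by eligibility and leaves only some 20 to 40 comparable infants

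*Protocol article*

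**What the plan says.** The Statistical analysis section of the protocol article treats the two nested programmes in one sentence: "For the PACT Online and LEAP programmes, effectiveness will be investigated using mixed effects models with programme participation included as the main effect", with adjustment for baseline factors. If families who take part differ from those who do not, propensity-based methods are to correct for it. Eligibility, referral and uptake will be summarised descriptively, and the sensitivity of comparisons such as uptake against non-uptake will be examined.

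The Data collection section shows that the two programmes differ in kind. PACT Online is offered to parents at 3 months corrected age, and any family can self-refer at any time. LEAP is a randomised trial with a health advice comparator, and its referral is conditional: "For infants aged <12 months CA in the study who have a high chance of adverse neurodevelopmental disability". The examples given are cerebral palsy, autism and fetal alcohol spectrum disorder. The referral is an offer, so families may decline.

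The Sample size and statistical power section is about associations: "The sample size of 400 families followed prospectively was chosen to provide sufficient power to examine associations" between perinatal factors and outcomes. It gives one relevant rate: "Assuming approximately 5% of the cohort will have the primary outcome", a composite worded as a chance of cerebral palsy, autism spectrum disorder or neurodevelopmental outcome. For continuous outcomes it claims detection of differences above 0.3 SD, and it adds that "repeated measurements over time and mixed-effects models will further improve precision". The article gives no LEAP eligibility rate, uptake, allocation ratio or detectable effect.

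**The concern.** A participation effect makes sense for a programme that any family may join. For LEAP it does not isolate the programme's effect, for three reasons.

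- **Eligibility.** LEAP participants are by definition infants flagged as having a high chance of disability. Infants who were not flagged have no possibility of taking part, so no propensity weight or match can make them stand in for participants.
- **Randomisation.** Participation is not defined. If it means enrolment in LEAP, it pools the LEAP and health-advice arms. If it means receiving the active programme, the health-advice arm is mixed with families who were never eligible or who declined. Under neither reading is the randomised contrast the one estimated.
- **Size.** Once the comparison is restricted to infants who could have been randomised, few remain.

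The study's stated goal is to inform policy and practice. An unfavourable participation estimate could merely reflect that LEAP infants were at higher risk from the start. A null from a few dozen infants could be taken as evidence against a family support programme. Neither reading would be justified.

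**Working it through.** **Inputs from the article:** 400 families; about 5% with the primary outcome; 80% power; α = 0.05; detectable differences of 8 percentage points (binary) and 0.3 SD (continuous).

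**Assumptions made here:** two-sided tests; LEAP eligibility near the primary-outcome rate; 1:1 allocation; full uptake and no dropout unless stated.

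**1. The plan's own figures.** With 200 v 200 and 5% v 13%, the pooled proportion is 0.09.
- SE under the null: √(2 × 0.09 × 0.91 / 200) = 0.0286.
- SE under the alternative: √((0.05 × 0.95 + 0.13 × 0.87) / 200) = 0.0283.
- Power: Φ((0.08 − 1.96 × 0.0286) / 0.0283) ≈ 0.80, so the stated 80% reproduces.
- Continuous outcomes: (1.96 + 0.84) × √(2/200) = 0.28 SD, in line with 0.3 SD. Detecting exactly 0.3 SD needs 175 per group.

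The 80% reproduces with 5% as the rate in the reference group. The overall rate is then (5% + 13%) / 2 = 9%. If 5% is instead the cohort-wide rate with equal groups (1% v 9%), power is 96%. Both 5% and 9% are carried forward.

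**2. Size of the comparable group.** 400 × 5% = 20 infants (binomial 95% range 12 to 29). 400 × 9% = 36.

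**3. Detectable difference between randomised arms**, one unadjusted measurement, 80% power: (1.96 + 0.84) × √(1/n₁ + 1/n₂), checked with the noncentral t.

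| Infants | Arms | Normal | t |
|---|---|---|---|
| 16 (20% loss or refusal from 20, assumed) | 8 v 8 | 1.40 SD | 1.51 SD |
| 20 (5%) | 10 v 10 | 1.25 SD | 1.32 SD |
| 36 (9%) | 18 v 18 | 0.93 SD | 0.96 SD |
| 40 (10%) | 20 v 20 | 0.89 SD | 0.91 SD |

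The 95% CI half-width at 10 v 10 is 2.10 × √(2/10) = 0.94 SD. To detect 0.5 SD, 126 infants are needed, or 31.5% of the cohort.

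**4. Allowing for the planned model.** With baseline adjustment and k averaged follow-up measures at common correlation ρ, the difference in step 3 is multiplied by √((1 + (k − 1)ρ)/k − ρ²). The article gives no correlation.
- k = 3, ρ = 0.5: factor 0.645, so 1.25 × 0.645 = 0.81 SD at 10 v 10.
- k = 8, ρ = 0.7: factor 0.497, so 1.25 × 0.497 = 0.62 SD at 10 v 10.
- The same factors at 18 v 18 give 0.93 × 0.645 = 0.60 SD and 0.93 × 0.497 = 0.46 SD.

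**5. The participation contrast.**
- *Against the whole cohort (20 v 380):* (1.96 + 0.84) × √(1/20 + 1/380) = 0.64 SD. This looks better than step 3 but estimates something else. If LEAP had no effect and flagged infants differed from the rest by 0.64 SD because of what led to their being flagged, this contrast would be significant about 80% of the time, unless baseline covariates removed the gap.
- *Uptake against non-uptake among 20 eligible infants:* 1.32 SD at 10 v 10 and 1.66 SD at 16 v 4. Eligibility is now balanced, but families select themselves and the randomised arms remain pooled.

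**The case against.** The strongest reply is that the article promises no power for this analysis. The sample size rationale is confined to associations, programme effectiveness is not among the three numbered aims in the Introduction, and LEAP is described as a randomised trial with its own ethics approvals. Expected numbers for a nested analysis can properly sit in a fuller document. This stands: low power for LEAP is not in itself an error in the article.

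A reader might also infer that at most 20 infants can be eligible, that only effects above 1 SD are detectable, or that the analysis cannot answer its question at all. The documents do not support these readings:

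- The 5% is the primary-outcome rate. LEAP eligibility is a similar but separate criterion that also names fetal alcohol spectrum disorder, and its rate is not given. Twenty is an illustration, not a ceiling.
- The 1 SD threshold holds for one unadjusted comparison at 10 v 10. Eighteen per arm, or the planned adjusted repeated-measures model, goes below it.
- A null result is very likely only for small effects. At 10 v 10 a single unadjusted test has 10% power for 0.3 SD but 40% for 0.8 SD and 56% for 1 SD.

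It can also be said that the plan already proposes propensity methods, sensitivity checks and descriptive uptake summaries. These help within the eligible group. They do not repair a contrast with infants who could never take part, and they do not bring in the randomisation.

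**Conclusion.** The concern holds as a matter of which contrast is fixed. For LEAP, a participation main effect with propensity correction is confounded by eligibility if made against the rest of the cohort, and by self-selection if made among the eligible. In neither case does it use the randomised comparison that the article itself describes.

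The number of comparable infants is roughly 20 to 40 if eligibility lies between 5% and 10%. With 1:1 allocation, a single unadjusted arm comparison then detects about 1.3 SD at 10 v 10, 0.96 SD at 18 v 18 and 0.91 SD at 20 v 20. At 10 v 10, baseline adjustment and repeated measures might bring this to 0.6 to 0.8 SD under assumed correlations, which is still at least twice the 0.3 SD quoted for the cohort. The eligibility rate, allocation, uptake and correlations are all assumptions. The confounding argument depends on none of them.

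PACT Online is open to all parents, so the eligibility argument does not reach it.

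**What to change.** In Statistical analysis, take LEAP out of the sentence it shares with PACT Online and give it its own. For example: among SFS infants randomised in LEAP, the difference between randomised arms will be reported with a 95% confidence interval, adjusted for baseline; this analysis is exploratory and no conclusion on effectiveness will be drawn from it. Keep the planned eligibility, referral and uptake summaries beside it. Leave the participation model and propensity methods for PACT Online.

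In Sample size and statistical power, add that the 0.3 SD figure does not apply to the LEAP analysis.

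The cost is wording, plus confirming that the planned linkage with the LEAP team carries the randomised allocation, which the article does not say. The downside is that SFS gives up a stand-alone claim about LEAP effectiveness. The analysis need not be deleted. Nor should the text say that SFS infants feed LEAP's own trial analysis, since the article describes the linkage only as serving analysis within SFS.

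### LEAP is described as a randomised trial, but its effectiveness is to be estimated from programme participation with propensity adjustment, without using or citing the randomised arms

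*Protocol article*

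**What the plan says.** The Data collection section of the protocol article gives the two nested programmes different designs.

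- LEAP: "LEAP is a randomised early support trial delivered in the home by Indigenous family support workers". The comparator follows: "Compared with a health advice programme, it includes goal-directed skill training". Entry is restricted: "For infants aged <12 months CA in the study who have a high chance of adverse neurodevelopmental disability". It is the families of these infants who may be referred, and they can decline.
- PACT Online: "This programme is directly offered to parents at 3 months CA, but families can self-refer at any point during the study". No randomisation is described.

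The Statistical analysis section gives both programmes one rule: "For the PACT Online and LEAP programmes, effectiveness will be investigated using mixed effects models with programme participation included as the main effect". Baseline covariates also enter the model. Participating and non-participating families are then to be compared on their characteristics, with weighting or propensity matching if they differ. Eligibility, referral and uptake are to be summarised descriptively, and the sensitivity of observational comparisons, such as uptake against non-uptake, is to be assessed. The section does not mention LEAP's allocated arm, does not say what counts as participation, and does not restrict the LEAP comparator to eligible or referred infants.

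**The concern.** PACT Online is open to all parents and entered by choice, so an observational model is the only one available for it. LEAP is different. Among enrolled infants, a comparison protected by randomisation exists, and the stated analysis does not use it.

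Three problems follow if the text is applied as written.

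1. **Indication.** Infants are referred to LEAP because they show signs of adverse neurodevelopment. That criterion overlaps closely with the cohort's primary outcome, the chance of cerebral palsy, autism or a neurodevelopmental outcome. A comparison with families outside LEAP mixes the programme effect with the reason for referral.
2. **Positivity.** Under the described pathway, an infant without such a finding is not offered LEAP. The probability of participation is then zero, and no weight can balance that infant against a participant.
3. **Exposure.** If participation means enrolment in LEAP, families allocated to health advice are coded as exposed.

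The likely error is that LEAP appears harmful or useless for child development when it is neither, in a study intended to inform policy.

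**Working it through.** **The plan's own figure.** The Sample size and statistical power section gives no figure for LEAP or PACT Online. Its cohort figure (400 families, outcome about 5%, 80% power, alpha 0.05, 8 percentage points) can be reproduced as 5% against 13% in equal groups, two-sided, with pooled variance:

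n = [1.96·√(2·0.09·0.91) + 0.842·√(0.05·0.95 + 0.13·0.87)]² / 0.08² ≈ 200 per group, 400 in total, power 80.1%.

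Nothing below depends on that result. It does show that 5% is not a ceiling: on this reading the overall rate is 9%, or 0.09 × 400 = 36 infants.

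**What the participation contrast would show if LEAP did nothing.** From the document: N = 400. Assumed: flag rate f of 5%, 10% or 20%; uptake 70%; flagged infants D SD lower; unit SD; all other families as comparator; no adjustment.

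- Flagged k = 400f; participants p = 0.7k; others q = 400 − p; flagged among others = 0.3k
- Contrast = −D + D·(0.3k/q)
- SE = √(1/p + 1/q)
- False rejection = Φ(|contrast|/SE − 1.96)

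| f | p | q | Flagged among others | SE | Contrast, D = 0.5 | False rejection | Contrast, D = 1.0 | False rejection |
|---|---|---|---|---|---|---|---|---|
| 5% | 14 | 386 | 6 | 0.272 | -0.49 | 44% | -0.98 | 95% |
| 10% | 28 | 372 | 12 | 0.196 | -0.48 | 69% | -0.97 | 100% |
| 20% | 56 | 344 | 24 | 0.144 | -0.47 | 90% | -0.93 | 100% |

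Almost the whole deficit of the flagged infants is attributed to the programme.

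**Dilution, if participation means enrolment in either arm.** With 1:1 allocation (assumed) and no effect of health advice, half of the participants receive the programme. A true effect δ then appears as 0.5δ.

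**What the randomised contrast could detect.** With m infants per arm, 1:1 allocation assumed, 80% power and two-sided 0.05, the detectable difference is (1.96 + 0.842)·√(2/m).

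| f | Uptake 100%: m, detectable | Uptake 70%: m, detectable |
|---|---|---|
| 5% | 10, 1.25 SD | 7, 1.50 SD |
| 10% | 20, 0.89 SD | 14, 1.06 SD |
| 20% | 40, 0.63 SD | 28, 0.75 SD |

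The article gives no flag rate, uptake or allocation ratio, so these are ranges, not predictions.

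**The case against.** LEAP is a separate trial. The Ethics and dissemination section lists its own approvals, and an arm-based analysis may well sit in LEAP's protocol, which is not shown. A reader might infer that the randomisation is lost altogether; the article does not support that. What stands is narrower: this article commits the cohort study to its own LEAP effectiveness analysis, and that analysis neither uses nor refers to the arms.

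A reader might also infer that flagged infants will definitely be compared with unflagged ones. The text permits this, and it is the plain reading of a comparison between participating and non-participating families, but the comparator is not defined. The mention of uptake against non-uptake could mean referred families who accept or decline. Including the flag in the propensity model and matching on common support would lead to the same place by dropping unflagged infants. Positivity is then restored and most of the indication bias in the table disappears. Self-selection still replaces randomisation.

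Likewise, pooling of the arms is a possible reading rather than a stated rule, since participation could be limited to families who receive the active programme.

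The section does recognise that uptake comparisons are observational and plans to assess their sensitivity. That does not supply the randomised contrast. Finally, programme effectiveness is not among the three associations that the Introduction sets as aims, and it is not powered. This makes the analysis ancillary, but not correct.

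**Conclusion.** The point holds in limited form. The article calls LEAP randomised, then fixes a participation-based, propensity-adjusted model for its effectiveness, shared with a programme for which no randomisation is described. This is a stated analysis choice, not detail left to a fuller document. On the broad reading, the contrast is confounded by indication, lacks positivity and may count health-advice families as exposed. On the narrow reading, it still sets a self-selected comparison in place of a randomised one.

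The biases of -0.47 to -0.49 SD (D = 0.5) and -0.93 to -0.98 SD (D = 1.0) apply to the broad reading only and rest on the assumed deficit, 70% uptake and no adjustment; the planned adjustment could reduce them. It would be tempting to cap LEAP enrolment at 20 infants from the 5% figure. The article does not support this, because 5% is an approximate outcome rate and no referral rate is given. Over flag rates of 5% to 20% and uptake of 70% to 100%, there would be about 7 to 40 infants per arm, and a detectable effect of about 0.6 to 1.5 SD.

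**What to change.** In the Statistical analysis section, separate the two programmes.

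- **LEAP:** estimate the effect by randomised arm, by intention to treat, among cohort infants enrolled in LEAP, or refer to the LEAP trial's own randomised analysis. Report an estimate with confidence interval and make no stand-alone effectiveness claim from the cohort.
- **LEAP uptake:** define participation. Restrict any comparison of uptake with non-uptake to eligible or referred infants, and label it observational.
- **PACT Online:** keep the participation model with weighting or propensity methods.

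The cost is mainly wording. The Data collection section already plans linkage with the LEAP team but does not list the linked variables, so the arm allocation may have to be requested. The price is a small and imprecise LEAP estimate.

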#### Recruitment

Initial recruitment will begin in Brisbane in mid-2026, followed by rollout to other sites shortly thereafter. Recruitment will be conducted through antenatal clinics at the listed study sites, employing a range of methods including flyers/posters, newsletters, social media and websites of partner organisations. Where feasible, experienced Indigenous health team members, such as midwives, Indigenous research assistants and Aboriginal health workers, will identify and approach potential pregnant individuals and their partners (if applicable).

Recruitment at hospitals will involve the screening of medical records to assess potential participants’ eligibility based on the study criteria, particularly that the mother is carrying an Indigenous infant in her pregnancy. This process will also ensure care is taken not to contact individuals who may have recently experienced an unexpected or adverse pregnancy complication, eg, miscarriage, stillbirth, termination or fertility issues, as this could trigger discomfort or emotional distress. Potential participants will be contacted either face-to-face, via phone or email. Those who express interest in the SFS will receive a Participant Information Sheet and Consent Form (PICF), along with a link to access the SFS Participant Information Video. An Indigenous member of the study staff will then arrange to discuss the study in detail and address any questions, preferably in a face-to-face setting. Potential participants will be advised that participation in the study is entirely voluntary, and individuals can withdraw at any time. The consent process will also explain the nested family support programmes, and parents will have the option to self-refer at any time and allow data linkage with SFS. The written consent of the pregnant participant will include the consent of her infant/young child. Parental/guardian consent may be sought from some young participants (between 16 and 18 years) if deemed necessary by the research team, but only when the youth provides verbal consent to participate in the study. Consent will be obtained in a culturally sensitive manner, including the use of a Participant Information Video recorded by ISC members and the study team, prepared using accessible language to support potential participants who may appreciate support in understanding the complexity of the study.

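### PACT Online is judged by comparing participating with non-participating families, adjusted for baseline factors and weighted only if differences appear, although uptake is staggered and plausibly follows need that arises after baseline

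*Protocol article*

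**What the plan says.** The Statistical analysis section covers both nested programmes in one paragraph. Effectiveness will be studied by mixed models, with "programme participation included as the main effect and models adjusted for baseline factors". The comparison is between families: "Differences in characteristics of families who do and do not participate in the programmes will be assessed". Weighting depends on what that assessment shows: "If any differences exist, they will be adjusted for in analyses using weighting methods such as propensity matching". The paragraph then promises descriptive reporting of eligibility, referral and uptake, and a further check: "The sensitivity of observational comparisons (eg, uptake vs non-uptake) will be assessed".

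The entry route is described elsewhere. Data collection says of PACT Online: "This programme is directly offered to parents at 3 months CA, but families can self-refer at any point during the study". Recruitment repeats that "parents will have the option to self-refer at any time and allow data linkage with SFS". The programme is aimed at parents' own state: "A parenting support programme will be offered that focuses on social and emotional well-being called PACT Online". Study regimen adds that infants with a confirmed or high chance of disability are referred to the study's support programmes. Data collection says that parents' samples and questionnaires are reviewed regularly to guide referral. Follow-up runs from pregnancy to age 5 (Abstract).

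**The concern.** Two features of the design do not fit the stated model.

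- **Staggered uptake.** A family may join PACT Online in the first months after birth or years later. A participant therefore contributes visits before joining as well as after. A single family-level participation term has no start date, so it averages over both kinds of visit unless the exposure is tied to the date of uptake.
- **Uptake driven by later need.** A parent whose mood worsens in the second year, or whose child is flagged then, is more likely to join. Factors measured at enrolment in pregnancy do not carry that information. Baseline adjustment leaves this confounding in place, and so does weighting on baseline characteristics.

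The rule for weighting adds to this. Making confounder control depend on a visible difference means that a real imbalance can pass unadjusted when few families take up the programme.

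At stake is the reading of a support programme in a study meant to inform policy. If struggling families are the ones who use it, it can look ineffective or harmful for that reason alone.

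**Working it through.** **1. The plan's own figures.** The article gives no power figure for PACT Online. Its cohort figures reproduce:
- Binary: 200 v 200, 5% v 13%, two-sided 0.05 (sidedness assumed) gives power 0.801, against the stated 80%.
- Continuous: (1.96 + 0.84) × √(2/200) = 0.28 SD for equal groups. For a 30:70 split (120 v 280), 2.80 × √(1/120 + 1/280) = 0.306 SD. Both fit the stated 0.3 SD.

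The 0.3 SD is used below as a yardstick for an effect worth detecting.

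**2. Dilution if participation is coded ever/never.** Let f be the share of participants' visits before uptake (assumed, since the article gives no uptake pattern). With uptake unrelated to distress, the expected estimate is effect × (1 − f), and the sample needed rises by 1/(1 − f)².

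| f | 0.30 SD becomes | required N multiplied by |
|---|---|---|
| 10% | 0.27 | 1.23 |
| 20% | 0.24 | 1.56 |
| 30% | 0.21 | 2.04 |
| 40% | 0.18 | 2.78 |
| 50% | 0.15 | 4.0 |

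**3. Need-driven uptake after baseline.** Simulation, 60 runs per scenario. The documents supply only the 400 families and, in outline, the visit schedule. Assumed:
- 10 post-birth visits from 6 weeks to 60 months.
- Outcome is a distress score with unit variance, 0.4 stable between families and 0.6 varying over time (correlation 0.6 between successive visits).
- Uptake possible before each visit, more likely around 3 months, with log-odds rising by 0, 0.5 or 1.0 per SD of the last distress score.

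This gave 47–54% ever taking up the programme and about 30% of participants' visits before uptake. Both models had a random family intercept, visit effects and the baseline outcome as covariate.

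| true effect | log-odds per SD | ever/never estimate | coded from uptake |
|---|---|---|---|
| −0.30 | 0 | −0.19 | −0.29 |
| −0.30 | 0.5 | −0.01 | −0.29 |
| −0.30 | 1.0 | +0.16 | −0.29 |
| 0 | 0 | 0.00 | 0.00 |
| 0 | 0.5 | +0.20 | +0.01 |
| 0 | 1.0 | +0.37 | +0.03 |

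A positive value is apparent harm. In the last two rows, a programme with no effect looked significantly harmful in 90% and 100% of runs under ever/never coding. The last column is no proof that re-coding is enough: its false-positive rate at a zero effect was 15–20%. It was already 18% with no confounding, which reflects serial correlation that the model ignores.

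**4. Other mechanisms.** A second simulation with other assumed inputs, again adjusting for the baseline outcome, gave ever/never estimates for a true −0.30 of −0.16 (random uptake), +0.11 (stable family distress) and +0.12 (last-score distress). At a true zero with distress-driven uptake it gave +0.25 to +0.30. A purely within-family estimate overstated benefit when uptake followed the last score: −0.07 at a true zero and −0.39 for a true −0.30. This is regression to the mean after a bad visit.

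**5. The conditional trigger.** Suppose 40 families use the programme and 360 do not (assumed), and a difference is judged by a 5% test (also assumed). A true imbalance of 0.3 SD gives 0.3 × √(40 × 360/400) = 0.3 × 6 = 1.8. Power is then Φ(1.8 − 1.96) = Φ(−0.16) = 0.44, so the imbalance would be missed more often than found.

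**The case against.** The strongest reply is that the article never says participation is constant over time. A main effect names the term of interest and not its coding. Linkage with the PACT Online team is planned at regular intervals, which should make start dates available, and an unseen analysis plan could define a time-updated exposure. Baseline might also mean the start of the programme. A reader might infer from the wording that visits before uptake are counted as treated. The documents do not say so, and the dilution in step 2 is conditional on that coding.

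Other parts of the reply also stand. Baseline adjustment is unconditional, and only the extra weighting waits on a difference. The authors call the comparison observational and plan to examine its sensitivity. No significance test is tied to the weighting rule, so the 0.44 only illustrates the risk. Uptake share, strength of self-selection and effect size are all assumed. In one check with stable family distress and a true −0.30, the ever/never estimate moved from +0.36 unadjusted to +0.10 with one baseline score and about +0.01 with the mean of two. The size, and whether the sign reverses, therefore depend heavily on the adjustment.

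What the reply does not remove is the mismatch in what the article does fix. It contrasts families who do and do not participate, it limits the stated model adjustment to baseline factors, and it makes weighting conditional. Any-time self-referral and referral on later findings create confounding after baseline, which none of these addresses. The sensitivity assessment has no named method, and its example repeats the same contrast.

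**Conclusion.** The concern holds in a limited form. The stated adjustment set and the conditional weighting rule do not suit a programme that families can enter at any time and plausibly enter because of need. If participation is coded ever/never, visits before uptake also dilute the effect. Under the assumptions shown, a true benefit of 0.30 SD can be halved (f = 50%) or can appear as harm of up to 0.16 SD.

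A reader might go further and conclude that the planned estimate will have the wrong sign. The documents do not support that: they give no uptake rate and no strength of self-selection, and they leave the coding open. Need-driven uptake is itself an inference, though the entry routes make it likely. The point is confined to PACT Online. LEAP shares the analysis paragraph but is described as a randomised trial with referral before 12 months corrected age. PACT Online is a nested, secondary evaluation, and the cohort's sample size does not rest on it. This should be corrected, but it does not undermine the main study.

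**What to change.** Amend the programme paragraph in Statistical analysis, for PACT Online, as follows:

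- Code participation from each family's programme start date, obtained through the planned linkage, and include visit effects.
- Adjust or weight using covariates and the outcome measured up to the visit before uptake. Inverse-probability or overlap weights would serve, as would a sequential comparison of families starting the programme with families not yet participating at the same visit.
- Fix this adjustment in advance and always apply it, whether or not differences are seen.
- Report a within-family estimate as a named sensitivity analysis and not as the main result, because alone it is biased when uptake follows transient distress.

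The cost is analysis wording, somewhat more modelling and slightly wider intervals. The change needs no visits, measures or families beyond those already planned.
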